## Abstract

**Background:**

Early childhood developmental delay is associated with significant disadvantage in adult life. In Pakistan, high prevalence of developmental delay is associated with poverty, under-nutrition, and maternal depression.

**Aim:**

To assess the effectiveness of an early child development counselling intervention delivered at private GP clinics, in poor urban communities.

**Design & setting:**

A clustered randomised trial in Pakistan.

**Method:**

The intervention was developed following a period of formative research, and in consultation with local experts. A total of 2112 mother–child pairs will be recruited at 32 clinics, from within the locality (cluster); 16 clinics per arm. A primary care counselling intervention (promoting child development, nutrition, and maternal mental health) will be delivered at 6 weeks, 3, 6, and 9 months of the child’s age. Monitoring, assessment, and treatment will also be performed at quarterly visits in intervention clinics. Primary outcome is the developmental delay at 12 months (ASQ-3 scores). Secondary outcomes are stunting rate, and maternal depression (PHQ-9 score). In addition, a process evaluation and costing study will be conducted.

**Discussion:**

This trial will be the first to assess an early child development intervention, delivered in private GP clinics for poor urban communities in Pakistan. If found to be effective, this public–private model may offer a more sustainable, and feasible option for populations in poor urban settings, where private GP clinics are the most accessible provider of primary health care. There is scope for scale-up at provincial level, should the intervention be effective.

**Trial registration:**

The trial has been registered with the Current Controlled Trials ISRCTN48032200.

## How this fits in

In Pakistan, the current mother and child care at private GP clinics does not cover the child brain development and mother mental health components, and nutrition counselling is also suboptimal, mainly due to lack of context-sensitive tools and inadequate staff ability and engagement. The referral linkages with public hospitals are also inadequate for mothers to access an expert consultation for their child development challenges. The intervention offers a set of primary care guidelines and tools for sustainable district health stewardship of private GP clinics to promote optimal early development of urban poor young children (that is, first year of life), through an integrated package of mother and child care. These women currently fail to access early child development care because of overloaded public hospitals, the inability of unregulated private clinics, and lack of affordability. This ‘action’ will solve the problem by making early child development care package available at selected private GP clinics. The care package will have three main components: nutrition, child development, and maternal mental health.

## Introduction

Childhood developmental delay is associated with poor subsequent educational attainment, and lower income during adult life, contributing to a cycle of poverty. It is a significant public health concern in many low- and middle-income countries, including Pakistan.^1^

Prevalence of developmental delay in Pakistan has been estimated at around 15%,^2^ even exceeding 30% among children from poorer families.^3^ Developmental delay is strongly linked to undernutrition,^4–6^ and maternal depression.^7^ Indeed, inadequate stimulation in early childhood, and maternal emotional characteristics, are associated with poorer cognitive development.^4^ In one Pakistani study more than one-quarter of new mothers had depression.^8^

There is evidence from low resource settings that programmes to improve infant stimulation and enhanced parenting skills have a beneficial effect on development.^9–11^ In the Caribbean, a parenting intervention integrated into routine primary care was effective in improving cognitive development.^12^ In Pakistan, a development and nutrition intervention delivered by community ‘lady health workers’ in Sindh province, had a significant positive effect on development outcomes.^13^

In poor urban areas of Pakistan, public primary care services are scant, and referral hospitals difficult to access due to distance, expense, and high demand. Primary care is therefore commonly provided by private GP clinics and small community hospitals. These are unregulated, unsupported, and vary in both quality and cost of services. Existing maternal and child health services do not adequately meet the early child development and maternal mental health needs of the population, and nutritional counselling is lacking.^14^ This trial has been designed to investigate the effectiveness and feasibility of integrating an early child development intervention into existing private GP clinic services for poor urban communities, and the aim will be to assess the effectiveness of a primary care intervention in reducing early developmental delay, in poor urban communities of Pakistan, using public–private partnership.

## Method

### Study design

Pragmatic, parallel arm, clustered randomised controlled trial with two arms (intervention and control) will be conducted to compare an early child development intervention delivered in private urban GP clinics in Pakistan, with usual routine care. Thirty-two clusters will be randomised using a 1:1 ratio, to intervention or control Figure 1.

**Figure 1. fig1:**
[figure not shown]
Trial flow diagram

### Setting

The districts of Lahore and Rawalpindi are study sites, following consultation with the Directorate General Health Services (DGHS), Children’s Hospital, and the Institute of Psychiatry. Lahore and Rawalpindi have large urban poor communities, and an extensive existing network of private GP clinics and small private hospitals. Average household size is 7.2 and 6.5 in Lahore and Rawalpindi respectively. Female literacy is around 60% in both districts. Electricity is available to more than 90% of households, but piped water to only 75% and 41% in Lahore and Rawalpindi respectively (and gas for cooking, 63% and 53%).^15,16^

### Clusters

Each trial cluster will represent one priority poor urban locality settlement, with limited access to a public hospital, and an average population of 50 000.

### Trial clinics

Within each cluster, one study clinic will be selected from available private GP providers, with preference for longer established clinics, and existing providers of maternal and child care. Private clinics typically comprise one doctor (GP), and employ at least one clinic assistant. Clinic assistants are usually males from the local area, with between 10–12 years of schooling, but no formal paramedic training.^14^ They are trained on-the-job by the private doctor, and support the private doctor by dispensing medication and performing other tasks, as necessary.

### Recruitment of mother–child pairs

Eligible mother child pairs will be recruited at participating private clinics by clinic assistants trained in trial recruitment and consent procedures. Recruitment will continue up to 6 weeks of child’s age, to allow for cultural restrictions during first 40 days postpartum.

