#### Exclusion criteria

Prematurity (<36 weeks gestation), history of congenital abnormality, delayed cry at birth, seizures, cretinism, or low birth weight (<2500 g)Mother intends to move out of area during study periodChild not accompanied by mother (for example, accompanied by another relative)

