#### Maternal counselling (core intervention)

A quarterly maternal educational counselling session with the clinic assistant at the private GP clinic will promote early child development, nutrition, and maternal mental health. Counselling content is developed from existing guides, in consultation with technical experts,^17,18^ supported by a pictorial flipbook.

Counselling will encourage mothers to engage in activities, appropriate for the expected stage of child development. It will also focus on nutrition and maternal mental health messages. Content was adapted for the context in Pakistan through a process of expert consultation. Trained and experienced artists were engaged to illustrate key activities and messages. The pictorial flipbook is two-sided: one side with pictures of activities to be shown to the mother; and the other with prompts for the clinic assistant. Each counselling session comprises 4–5 pages of the flipbook, and takes no more than 10 minutes to deliver.

Mother–child pairs will be invited to return for follow-up every 3 months, to receive the next counselling session; that is, at 6 weeks, then at 3, 6, and 9 months of the child’s life.

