A logic model and theory of change for the intervention is described in Box 2, drawing on the refined Theoretical Domains Framework.^21^

**Box 2. B2:** Logic model for proposed intervention mechanisms/theory of change (adapted from Bonell and colleagues 2015)^38^

	**Inputs**	**Processes and actions**	**Intended changes (Theoretical domains framework)^21^**	**Intended outputs**	**Intended health outcomes**
**Intervention**	Formative research: interviews with providers, mothers, and key stakeholders Consultation with experts to develop technical materials: • Training protocols and manuals • Counselling flipbook • Community advocate leaflets Training of private GPs and clinic assistants: theoretical and practical training	Quarterly counselling sessions for mothers (child development, child nutrition, maternal mental health) Quarterly child growth monitoring Text message/SMS reminders to mothers for quarterly follow-up appointments Assessment and treatment of chid developmental delay (may include referral) Assessment and treatment of maternal depression (may include)	**Mother** Social influences Knowledge Beliefs about consequences Environmental context and resources Reinforcement **Private GP and clinic assistant** Social influences Knowledge Skills Environmental context and resources Social and professional role and identity	**Mother** Mother–child health services are accessible and desirable to mother Increased capability and confidence to support child nutrition and development in the home environment Increased capability and confidence to protect own mental health in the home environment **Private GP and clinic assistant** Motivated and skilled to provide mother–child health services	Reduced developmental delay at 12 months of age (primary outcome) Improved childhood nutrition Reduced maternal depression
**Both intervention and control arms**	DGHS endorsement of intervention and control clinics Identification and orientation of community advocates Growth Monitoring Cards to intervention and control clinics Standard calibrated equipment to intervention and control clinics Supervision of data entry on Growth Monitoring Card by clinic assistant (Field research officer)	Recruitment of mothers by community advocates Vitamin A supplement		Adequate participant recruitment High quality data	

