#### Analysis

Both individual and cluster level analysis will be conducted according to intention to treat in SPSS version 20.0 and R version 3.2.3 respectively. Intervention and control arms will be compared at baseline to ensure equal distribution of potential confounders like maternal education, the purpose of randomisation. Scores will be calculated for the five domains of developmental delay namely gross motor, fine motor, problem solving, and personal–social using ASQ3. The two arms will be compared for these five domains of development delay at 12 months by independent sample *t*-test adjusting for clustered data, as used by other researchers,^34^ by applying t.test.cluster in Hmisc package in R. Stunting will be measured at end line using WHO Anthro SPSS Macros. The two arms will be compared with respect to stunting by χ^2^ test adjusted for clustering^35^ by applying donner function in aod package in R.^36^ Mother’s mental health condition will be compared across both arms as end line using PHQ-9 scores *t*-test adjusting for clustered data.^34^ A *P*-value <0.05 will be considered significant. Generalised estimating equation (GEE) and generalised linear mixed models (GLMM) will be applied using R packages gee and glmmML respectively in case of residual confounding.^37,38^

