#### Randomisation

Simple randomisation will be performed by drawing from a hat, by a member of the host research organisation not involved in the study. Stratification by districts (Rawalpindi and Lahore) has not been done as both share similar characteristics being major cities in the province of Punjab. Nevertheless clinic size, if not equally distributed between both arms by randomisation, will be taken care of in modeling (GEE and GLMM as mentioned above).

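### Pairs are enrolled by the clinic role that also delivers the counselling, very probably after allocation, so randomising clinics does not secure the balance of pairs that the Analysis section credits to it

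*Protocol article*

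**What the plan says.** - **Unit of randomisation.** Study design: "Thirty-two clusters will be randomised using a 1:1 ratio". Randomisation: "Simple randomisation will be performed by drawing from a hat, by a member of the host research organisation not involved in the study". Neither section says when the draw takes place relative to enrolment.
- **Who enrols.** Recruitment of mother–child pairs: "Eligible mother child pairs will be recruited at participating private clinics by clinic assistants trained in trial recruitment and consent procedures". Entry is open until the child is 6 weeks old.
- **Who treats.** Maternal counselling (core intervention): "A quarterly maternal educational counselling session with the clinic assistant at the private GP clinic". The sessions fall at 6 weeks and at 3, 6 and 9 months. Intervention assistants also monitor growth and give the PHQ-2.
- **Training.** Box 1 and Control clinics describe different training by arm. Intervention assistants learn the flipbook session, the PHQ-2, and length and weight measurement. Control staff learn the study forms and get a general overview.
- **Eligibility.** The exclusions include "history of congenital abnormality, delayed cry at birth, seizures, cretinism, or low birth weight" and a mother's intention to move away. No inclusion criterion requires residence in the locality, although the Abstract describes the pairs as "recruited at 32 clinics, from within the locality (cluster").
- **Blinding.** ASQ-3 assessors are blinded, at the 12-month outcome. No blinding of recruiters is described.
- **Baseline.** Analysis: the arms are to be "compared at baseline to ensure equal distribution of potential confounders like maternal education, the purpose of randomisation". GEE and GLMM are held back for residual confounding.
- **Limitations.** Strengths and limitations covers non-attendance, record keeping, fidelity and recall bias. It does not cover selective recruitment.

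**The concern.** In a cluster trial, randomisation makes the clinics and their localities comparable in expectation. It makes the enrolled pairs comparable only if pairs are identified before allocation, or enter in a way that knowledge of the arm cannot influence. Here the recruiter belongs to the clinic, holds the role that carries the intervention, and applies criteria that partly depend on what the mother reports. If intervention and control assistants enrol different kinds of mothers, the ASQ-3, stunting and PHQ-9 comparisons all inherit the difference.

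Intention to treat and adjustment for clustering do not address this. GEE or GLMM can correct only for characteristics that were recorded. Blinded ASQ-3 assessment acts at outcome, not at entry. A larger sample narrows the interval around a biased estimate.

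**Working it through.** **Step 1. Does enrolment follow allocation?** The article does not say, and Figure 1 is not reproduced in the text available. Two stated facts bear on it.
1. Training differs by arm, and control staff learn the study forms in their arm-specific session. Staff would therefore know the arm before using those forms.
2. Children enter at up to 6 weeks of age and the first session is due at 6 weeks. A cluster of 66 pairs that fills over time cannot be complete before the first pairs are due for counselling, so the arm must be known while enrolment is still running.

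Enrolment after allocation is thus a strong inference, not a quotation. An assistant trained to deliver the counselling cannot be blind to it.

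**Step 2. Is there room for selection?** Delayed cry, seizures and history of congenital abnormality depend largely on history, and intention to move depends on the mother's statement. These leave some discretion in who is declared eligible.

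**Step 3. What could it do?** The plan gives no figure for selection, so this step is illustrative. Inputs from Sample size calculation: 33% delay, 16 clusters of 66 per arm (16 × 66 = 1056, as stated), 10% loss, ICC 0.15. Whether 1056 follows from the stated effect is a separate question and is not needed here.
- Assessed per cluster: 66 × 0.9 = 59.4; per arm 16 × 59.4 = 950.4.
- Design effect: 1 + 58.4 × 0.15 = 9.76. Effective number per arm: 950.4 / 9.76 = 97.4.
- SE of the difference with no effect: √(2 × 0.33 × 0.67 / 97.4) = 0.0674.
- Suppose a share f of would-be delayed children is missed in one arm only. The rate there is 0.33(1 − f) / (1 − 0.33f). The values of f are assumptions.
- Two-sided rejection for a spurious difference b: Φ(b/SE − 1.96) + Φ(−b/SE − 1.96).

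| Assumed f | Rate in that arm | b (points) | Rejection at ICC 0.15 |
|---|---|---|---|
| 0 | 33.0% | 0 | 5.0% |
| 10% | 30.7% | 2.3 | 6.3% |
| 13% | 30.0% | 3.0 | 7.3% |
| 20% | 28.3% | 4.7 | 10.8% |

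The ICC of 0.15 is given for maternal education, not for delay. With b = 3 points, assumed ICCs of 0.05 and 0.03 give SEs of 0.0427 and 0.0358, and rejection of 10.8% and 13.4%.

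**Step 4. Can baseline data settle it?** Take female literacy of about 60% (Setting) and apply ICC 0.15 to 66 pairs per cluster. The design effect is 1 + 65 × 0.15 = 10.75 and the effective number is 1056 / 10.75 = 98.2. The chance SE of the difference between arms is √(2 × 0.6 × 0.4 / 98.2) = 0.070. Differences of up to about 1.96 × 7.0 = 14 points would arise without any selection, so a baseline table can neither prove nor exclude it.

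**The case against.** The strongest reply is that much of this is inference and that the article condenses a fuller protocol. The order of events is unstated. Clinics employ at least one assistant, so the overlap of recruiter and counsellor is documented for the role, not for the individual. Screening logs and recruitment rules are commonly left to the full document, and their absence here is no finding. All of that stands. What remains is the recruiting arrangement the article does state, and its stated reason for expecting balanced pairs.

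A reader might also infer more than the documents support:
- **That intervention assistants are trained to spot exclusions.** Their listed training covers none of the exclusion conditions, and management of developmental delay is taught to the GPs.
- **That missing records make birth history unverifiable.** The short retention described is usual practice, and both arms will be told to keep records.
- **That mothers choose their arm.** There is one study clinic per locality, and DGHS endorsement is the same in both arms.
- **That recruiters are contradictory or leaflets one-sided.** Box 2 has "Recruitment of mothers by community advocates", but Community advocates explains that advocates encourage participation and hand out leaflets. Box 1 gives advocates to both arms.
- **That poverty mix could shift the delay rate greatly.** The contrast between about 15% delay overall and over 30% in poorer families comes from two separately cited sources, while every cluster is a poor urban locality.
- **That workload drives selection.** This is possible but speculative, since a session takes no more than 10 minutes.

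**Conclusion.** The point holds in a limited form. Pairs are enrolled by the role that delivers the intervention, very probably with the arm known, so the mix of pairs can differ by arm. The Analysis section is wrong to treat balance of pairs as secured by randomising clinics, and the limitations should name the risk.

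Direction and size are unknown. Under an assumed 3-point spurious difference the 5% error rate becomes about 7% at the document's ICC. Three points is 15% of a 20-point target. Reading the target as a relative 20% (6.6 points) would make it 45%, but that reading needs roughly 8,156 to 8,983 pairs per arm against the 1056 planned. It would therefore go too far to say that a positive result could not be told apart from selection, or that cluster randomisation offers no protection: the comparison of clusters stays protected. The conclusion rests on the inferred order of allocation and enrolment, which Figure 1 or the full protocol could confirm or correct.

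**What to change.** 1. **Recruitment of mother–child pairs.** State when the draw occurs relative to enrolment. Enrol consecutive eligible pairs until the cluster target of 66 is reached. Use one identical screening log in both arms recording presented, eligible, offered and enrolled, with reasons for exclusion. The research officer who already checks completeness of data also checks the log.
2. **Training.** Give recruitment and consent training to all assistants together, before the draw. Use one arm-neutral eligibility script, completed with the baseline form before any arm-specific care begins. If the draw has already taken place, the log, script and wording changes still apply.
3. **Inclusion criteria.** Add residence in the clinic's locality, as the Abstract describes.
4. **Analysis.** Remove the claim that randomisation ensures balance of pairs. Report screening flow by arm. Describe baseline differences without treating them as proof of selection.
5. **Strengths and limitations.** List recruitment bias.

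The cost is one form per clinic, a re-ordering of planned training, protocol wording and slightly slower enrolment, with no extra staff or participants. The risk is reduced rather than removed, because recruiters remain unblinded.

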#### Inclusion criteria

Mother–child pairChild ≤6 weeks

#### Exclusion criteria

Prematurity (<36 weeks gestation), history of congenital abnormality, delayed cry at birth, seizures, cretinism, or low birth weight (<2500 g)Mother intends to move out of area during study periodChild not accompanied by mother (for example, accompanied by another relative)

### Intervention

The intervention was developed following a period of formative research.^14^ In brief, this focused on understanding the context within private GP clinics, and experiences and preferences of mothers. Feasibility and acceptability of proposed intervention components were explored, and findings used to inform intervention development. The outline is described in Box 1.

#### Maternal counselling (core intervention)

A quarterly maternal educational counselling session with the clinic assistant at the private GP clinic will promote early child development, nutrition, and maternal mental health. Counselling content is developed from existing guides, in consultation with technical experts,^17,18^ supported by a pictorial flipbook.

Counselling will encourage mothers to engage in activities, appropriate for the expected stage of child development. It will also focus on nutrition and maternal mental health messages. Content was adapted for the context in Pakistan through a process of expert consultation. Trained and experienced artists were engaged to illustrate key activities and messages. The pictorial flipbook is two-sided: one side with pictures of activities to be shown to the mother; and the other with prompts for the clinic assistant. Each counselling session comprises 4–5 pages of the flipbook, and takes no more than 10 minutes to deliver.

Mother–child pairs will be invited to return for follow-up every 3 months, to receive the next counselling session; that is, at 6 weeks, then at 3, 6, and 9 months of the child’s life.

